## Assessment of causality

Every effort should be made by the investigator to explain each adverse event and assess its causal relationship, if any, to administration of the study vaccine(s).

The degree of certainty with which an adverse event can be attributed to administration of the study vaccine(s) (or alternative causes, e.g. natural history of the underlying diseases, concomitant therapy, etc.) will be determined by how well the event can be understood in terms of one or more of the following:

- Reaction of similar nature having previously been observed with this type of vaccine and/or formulation.
- The event having often been reported in literature for similar types of vaccines.
- The event being temporally associated with vaccination or reproduced on re-vaccination.

All solicited local (injection site) reactions will be considered causally related to vaccination. Causality of all other adverse events should be assessed by the investigator using the following method:

In your opinion, did the vaccine(s) possibly contribute to the adverse event?

| NO | : | The adverse event is not causally related to administration of the study vaccine(s). There are other, more likely causes and administration of the study vaccine(s) is not suspected to have contributed to the adverse event. |
| --- | --- | --- |
| YES | : | There is a reasonable possibility that the vaccine contributed to the adverse event. |

Non-serious and serious adverse events will be evaluated as two distinct events given their different medical nature. If an event meets the criteria to be determined “serious” (see Section 8.5 for definition of serious adverse event), it will be examined by the investigator to the extent to be able to determine ALL contributing factors applicable to each serious adverse event.

Clinical laboratory parameters and other abnormal assessments qualifying as adverse events and serious adverse events

Abnormal laboratory findings (e.g., clinical chemistry, hematology, urinalysis) or other abnormal assessments (e.g. blood film) that are judged by the investigator to be clinically significant will be recorded as AEs or SAEs if they meet the definition of an AE, as defined in Section 8.1 or SAE, as defined in Section 8.5. Clinically significant abnormal laboratory findings or other abnormal assessments that are detected during the study or are present at baseline and significantly worsen following the start of the study will be reported as AEs or SAEs. However, clinically significant abnormal laboratory findings or other abnormal assessments that are associated with the disease being studied, unless judged by the investigator as more severe than expected for the subject’s condition, or that are present or detected at the start of the study and do not worsen, will not be reported as AEs or SAEs.

The investigator will exercise his or her medical and scientific judgment in deciding whether an abnormal laboratory finding or other abnormal assessment is clinically significant.

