# Part B: Indication/ Study Population

Healthy, malaria-experienced adults living in western Kenya aged 18-50 years

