## Eliciting and documenting adverse events

### Adverse event definition

An AE is any untoward medical occurrence in a study volunteer, temporally associated with the use of a test article, whether or not considered related to the test article. An AE can therefore be any unfavorable and unintended sign (including an abnormal laboratory finding), symptom, or disease (new or exacerbated) temporally associated with the use of a test article whether or not it is considered to be study related.

Examples of an AE include:

- Exacerbation of a chronic or intermittent pre-existing condition including either an increase in frequency and/or intensity of the condition.
- New conditions detected or diagnosed after investigational product administration even though it may have been present prior to the start of the study.
- Signs, symptoms, or the clinical sequelae of a suspected overdose of either investigational product or a concurrent medication (overdose per se should not be reported as an AE/SAE).
- Signs, symptoms temporally associated with vaccine administration.

AEs may include pre- or post-treatment events that occur as a result of protocol-mandated procedures (i.e., invasive procedures, modification of subject’s previous therapeutic regimen). Pre-existing conditions or signs and/or symptoms present in a subject prior to the start of the study (i.e. prior to the first study procedure) as well as any that are not recognized at study entry but are recognized during the study period, should be recorded in the medical history section of the subject’s CRF. Adverse events that occur after informed consent is obtained, but prior to vaccination, will be documented the Medical History form within the participant's CRF. Anticipated day-to-day fluctuations of pre-existing conditions, including disease under study, that do not represent a clinically significant exacerbation need not be considered adverse events. Adverse events should be documented in terms of medical diagnosis(ses) when possible. When this is not possible, the adverse event should be documented in terms of signs and symptoms observed by the investigator or reported by the participant at each study visit.

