Although not considered as an adverse event, hospitalization for either elective surgery related to a pre-existing condition that did not increase in severity or frequency following initiation of the study, or for routine clinical procedures (including hospitalization for “social” reasons) that are not the result of an adverse event, must be recorded in the CRF. If the hospitalization arises from a pre-existing condition, or was planned prior to the first vaccination, it should be recorded in the Medical History form of the CRF. If the hospitalization arises from a pre-existing condition, and the hospitalization was planned after the first vaccination, it should be recorded in the adverse event page of the CRF. In both cases, it should be recorded as ‘Hospitalization,’ and the relationship to vaccination will be checked “No.”

*Surveillance period for occurrence of adverse events*

All adverse events occurring within one month (minimum 30 days) following administration of each vaccine must be recorded on the Adverse Event form in the participant's CRF, irrespective of severity or whether or not they are considered vaccination-related. See Section 8.5 for instructions for recording and reporting of serious adverse events.

*Recording adverse events*

At each visit/assessment, all adverse events either observed by the investigator or one of his clinical collaborators or reported by the participant spontaneously or in response to a direct question will be evaluated by the investigator. Adverse events not previously documented in the study will be recorded in the Adverse Event form within the participant's CRF. The nature of each event, date and time (where appropriate) of onset, outcome, intensity, and relationship to vaccination should be established. Details of any corrective treatment should be recorded on the appropriate page of the CRF.

Adverse events already documented in the CRF, i.e. at a previous assessment, and designated as ‘ongoing’ should be reviewed at subsequent visits, as necessary. If these have resolved, the documentation in the CRF should be completed.

N.B. If an adverse event changes in frequency or intensity during a study period, the highest intensity will be recorded. If the adverse event recurs with a defined interval of symptom-free time (>24 hours) in between episodes, new record of the event will be started.

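### Section 8.3 keeps clinically significant laboratory or film findings linked to malaria off the AE/SAE record unless judged unexpectedly severe, contradicting the protocol's own AE and SAE rules

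*Protocol*

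**What the plan says.** The last part of Protocol Section 8.3 (Assessment of causality) says when laboratory findings and "other abnormal assessments (e.g. blood film" is the example given) become AEs or SAEs. It works in three steps.

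- Findings that the investigator judges clinically significant are recorded if they meet the AE definition in Section 8.1 or the SAE definition in Section 8.5.
- Clinically significant findings "that are detected during the study or are present at baseline and significantly worsen following the start of the study" are reported.
- Two kinds of clinically significant finding are then taken out. The first covers laboratory results as well as "abnormal assessments that are associated with the disease being studied, unless judged by the investigator as more severe than expected", with expected severity judged against the volunteer's own condition. The second is findings present at the start that do not worsen. Both "will not be reported as AEs or SAEs".

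The disease being studied is not defined. The synopsis gives the Part B population as "Healthy, malaria-experienced adults living in western Kenya aged 18-50 years".

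Section 8.1.1 defines an AE to include "any unfavorable and unintended sign (including an abnormal laboratory finding), symptom, or disease (new or exacerbated"), whether or not related to the test article. On surveillance it says: "All adverse events occurring within one month (minimum 30 days) following administration of each vaccine must be recorded", regardless of severity or relatedness. The SAE definition in Section 8.5.1 has no exemption for any disease.

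**The concern.** An exemption of this kind suits a trial in patients who enter with the disease under study, where its expected laboratory signs would otherwise fill the AE listing. Here the volunteers enter healthy and malaria is what they may acquire during follow-up. The clause then acts on new events rather than on a background condition.

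It also acts only on findings already judged clinically significant, since trivial ones are filtered out one step earlier. Once such a finding is attributed to malaria, it leaves the AE record unless the investigator calls it more severe than expected, and the protocol gives no reference for that judgement in a healthy person.

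At stake is the completeness of the AE record in a trial whose primary objective is safety. A finding that is not an AE is also never put to the Section 8.3 question of whether the vaccine possibly contributed. A later analysis cannot recover a causality judgement that was not made.

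**Working it through.** No figure in the plan bears on this point, so the check sets the provisions side by side.

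1. **Which disease?** The product is a candidate *P. falciparum* vaccine and no other disease is under study. Blood film is the named example of an assessment in scope. The clause can only sensibly refer to malaria.

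2. **Is there a condition to measure against?** No. Section 4.2 requires freedom from significant health problems. Section 4.3 excludes hemoglobin and platelet counts below the normal range. A low value in follow-up is therefore normally new.

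3. **Against the AE definition (8.1.1).** Abnormal laboratory findings and new disease count as AEs irrespective of relatedness. Section 8.3 first defers to that definition and then removes findings that satisfy it.

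4. **Against the recording rule (8.1.1).** All AEs within at least 30 days of each dose are recorded, irrespective of severity. Counting the dose day, the nominal windows are Days 0–29, 28–57 and 56–85 (56 + 29 = 85). They cover Days 0 to 85 without a gap. Section 5.5 schedules a blood count on Days 0, 7, 28, 35, 56, 63 and 112. The post-Dose 1 counts on Days 7, 28, 35, 56 and 63 fall inside this period, so a clinically significant, malaria-attributed finding there falls under two opposite instructions. Day 112 lies outside the 30-day rule, but its visit list also asks for unsolicited events since the last dose.

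5. **Against the SAE definition (8.5.1).** That definition turns on seriousness criteria alone. Section 8.3 says exempted findings are not SAEs either.

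6. **Against the other disease wording in 8.1.1.** That sentence excuses only anticipated day-to-day fluctuation of pre-existing conditions, and only when it is not a clinically significant exacerbation. The Section 8.3 clause is wider, because it excuses clinically significant findings and is not limited to pre-existing conditions.

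7. **Is the clause needed for baseline findings?** No. The second exemption in the same sentence already covers findings present at the start that do not worsen.

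8. **What stays captured?** A malaria diagnosis after dosing is a new condition and so an AE under 8.1.1, and an SAE under 8.5.1 if a seriousness criterion is met. Section 10.4.2 tabulates clinically relevant hematology and biochemistry values. Section 8.4 requires clinically significant laboratory abnormalities to be followed up alongside any AE.

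9. **What is left?** AE/SAE records, with their causality assessment, of malaria-associated abnormalities detected by laboratory or film. For scale only, one such volunteer is 1/20 = 5 percentage points of Group 3 or 1/10 = 10 points of Group 4.

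**The case against.** The strongest reply is that the clause does little harm. It covers laboratory findings and other assessments, not illness. Abnormal blood values are tabulated and followed up anyway. No blood film is in the visit schedule, so a positive film would come only from an unscheduled evaluation. Scheduled *P. falciparum* antigen detection is exploratory and depends on remaining sample. Section 8.1.3 describes unsolicited events as reported by the subjects, so a laboratory-only finding might fall outside that co-primary endpoint in any case. Such a finding would also rarely meet a seriousness criterion by itself.

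Most of this stands, and it sets the limits of the point. It does not remove the contradiction. The laboratory table in Section 10.4.2 names hematology and biochemistry, not films, and it is not the AE record. Follow-up under Section 8.4 does not supply the causality judgement.

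Three stronger readings are tempting and are not supported:

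- **That malaria episodes drop out of the safety data.** They do not: diagnoses, symptoms and hospitalizations remain reportable under Sections 8.1.1 and 8.5.1. The documents therefore do not show that the co-primary endpoints lose clinical malaria.
- **That the earlier Kenyan adult trial sizes the loss.** Section 1.3.2 reports mild anemia in 19 of 255 volunteers (10, 3 and 6 by arm). It links none of these cases to malaria and does not call them clinically significant. The vaccines were also different.
- **That the mention of the disease under study in Section 8.1.1 is equally faulty.** It reaches only fluctuations of pre-existing conditions that are not clinically significant, so a new malaria finding is unaffected.

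**Conclusion.** The point holds in a limited form. The Section 8.3 exemption contradicts Sections 8.1.1 and 8.5.1, and its severity test has no reference in healthy volunteers. Following it could leave clinically significant, malaria-associated laboratory or film abnormalities out of the AE/SAE record and its causality assessment, at the investigator's discretion.

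The size cannot be estimated, because the documents give no rate for such findings. The 5- and 10-point figures show what one volunteer is worth in groups of 20 and 10, not how often the rule would bite.

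The conclusion assumes that the undefined disease is malaria and that investigators apply the clause as written. It is a recording inconsistency worth correcting because the correction is simple. It does not mean that malaria is invisible in the safety data.

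**What to change.** Reconcile the laboratory part of Section 8.3 with Sections 8.1.1 and 8.5.1 in one of two ways:

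- delete the clause exempting findings associated with the disease being studied, keeping the exemption for findings present at the start that do not worsen; or
- keep the clause and state that it does not cover malaria-associated findings arising after Dose 1.

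The wording on day-to-day fluctuation in Section 8.1.1 can stay. The change concerns recording only and leaves clinical management untouched. It costs an amendment of one clause, or one added sentence, and a few more AE records.

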## Following-up of adverse events and assessment of outcome

Investigators should follow-up subjects with serious adverse events until the event has resolved, subsided, stabilized, disappeared, the event is otherwise explained, or the subject/patient is lost to follow-up; or, in the case of non-serious adverse events, the subject/patient completes the study. Clinically significant laboratory abnormalities, as well as any adverse event, will be followed up until they have returned to normal, or a satisfactory explanation has been provided. Reports relative to the subsequent course of an adverse event noted for any subject must be submitted to DHSP/WRAIR IRB.

Outcome should be assessed as:

1 = Recovered

2 = Recovered with sequelae

3 = Ongoing at subject study conclusion (active phase)

4 = Died

5 = Unknown

## Serious adverse events

### Definition of a serious adverse event

A serious adverse event (SAE) is any untoward medical occurrence that:

1. results in death,

b. is a life-threatening adverse drug experience,

c. requires hospitalization or prolongation of existing hospitalization,

d. results in a persistent or significant disability/incapacity, or

e. is a congenital anomaly/birth defect in the offspring of a study volunteer.

Medical or scientific judgment should be exercised in deciding whether reporting is appropriate in other situations, such as important medical events that may not be immediately life-threatening or result in death or hospitalization but may jeopardize the subject or may require medical or surgical intervention to prevent one of the other outcomes listed in the above definition. These should also be considered serious.

An unexpected or unanticipated adverse event is any adverse drug/test article experience, the specificity or severity of which is not consistent with the current investigator brochure or general investigational plan.

### Reporting serious adverse events

Serious Adverse Events will be reported in a prospective manner during the period starting from the day of administration of the first dose of study vaccine to each subject and ending with the last study. Unanticipated problems involving risk to volunteers or others, serious adverse events related to participation in the study and all volunteer deaths should be promptly reported by the investigator to the sponsor, KEMRI IRB, GSK Biologicals’ Clinical Safety Physician at [contact], [contact] or [contact]; or mobile phones for 7/7 day availability: [contact]; e-mail: [[contact]](mailto:[contact]) or Head Safety Evaluation and Risk Management, Adult/Adolescent/Emerging Diseases at [contact], or Head of Safety Evaluation and Risk Management, Pediatric, at mobile [contact] hour and 7/7 day availability) and to WRAIR IRB by [contact]), by email ([contact]), or by [contact]) to the Division of Human Subjects Protection, Walter Reed Army Institute of Research, [name]. WRAIR IRB will report to USAMRMC ORP/HRPO as per SOP UWZ-C-636 within 24 hours (one calendar day) of his/her becoming aware of the event. Such events should also be reported in a similar method to the U.S. Army Medical Research and Materiel Command’s Human Subjects Research Review Board (HSRRB) by [contact]) by email ([contact]) or by [contact]) and USAMMDA Regulatory Affairs Office ([contact], [contact] or via email [contact] ). The investigator will document all available information regarding the serious adverse event in the Serious Adverse Event pages contained in the individual case report form and FAX to the GlaxoSmithKline Contact for Serious Adverse Event Reporting.

A complete written report should follow the initial notification within three working days.  In addition to the methods above, the complete report can be sent to the Director, Division of Human Subjects Protection, Walter Reed Army Institute of Research, [name]., [name] 20910-7500 Room 1W30 and the U.S. Army Medical Research and Materiel Command, ATTN:  MCMR-ZB-P, [name]

The investigator should not wait to receive additional information to fully document the event before notifying GlaxoSmithKline Biologicals, or the USAMRMC Office of Research Protection (MRMCORP) and the USAMMDA Product Manager of a serious adverse event. This initial notification should give as minimum, sufficient information to permit identification of:

- The reporter
- The subject initials, identification number, date of birth, gender and ethnicity
- Study test article
- Date of administration
- Adverse events (Date of onset, signs/symptoms and severity)
- Action taken
- Concomitant medications (dose, route, duration)

In the event of a death or a serious adverse event determined by the investigator to be related to vaccination, receipt of the fax must be confirmed by a telephone call. The fax report should be followed by a full written report using either the GSK Biologicals Serious Adverse Events form or the US FDA MedWatch form, detailing relevant aspects of the adverse events in question. It should include copies of relevant hospital case records, autopsy reports, and other documents where applicable.

In the event that a serious adverse events determined by the investigator to be related to vaccination are detected following any vaccination in any of the vaccine groups, no further vaccinations will be administered until a written report has been submitted to KEMRI, the WRAIR IRB, HSRRB, USAMMDA Product Manager, and the FDA, and the investigators have conferred with the GSK, and WRAIR and/or USAMRU-K Medical Monitors.

If an instance of congenital abnormality in offspring is brought to the attention of the investigator at any time after cessation of study vaccine AND is suspected by the investigator to be related to study vaccine, it should be reported to the Study Contacts for Serious Adverse Event Reporting.

### Pregnancy

Subjects who become pregnant during the study period must not receive additional doses of vaccine, but may continue other study procedures to include blood draws for immunogenicity and safety and review of symptoms/physical exams for reactogenicity data, at the discretion of the primary investigator. Subjects will be instructed to notify the investigator if it is determined after completion of the study that they became pregnant either during the study or within 30 days of the study. Although not considered an adverse event, pregnancy will be reported in the same way as a serious adverse event (see Section 8.5.2).

A pregnancy will be followed to term. Any premature terminations will be reported, and the health status of the mother and child including date of delivery and the child’s gender and weight will be reported to DHSP/ WRAIR IRB, HSRRB, USAMMDA, KEMRI and GSK Biologicals after delivery.

### Treatment of adverse events

The PI, in conjunction with the medical monitor, will ensure each volunteer receives appropriate treatment of any adverse event related to the vaccine.

# SUBJECT COMPLETION AND DROPOUT

## Definition

A volunteer who has completed the study is one who receives all three doses of the vaccine and has had the required safety and immunogenicity evaluations. A dropout is anyone who has not completed the study. Reasons for dropout are listed in Section 9.3 below. Subject compliance for test article administration will not be an issue because the vaccine will be administered by study staff. The subject will be reminded by study staff and/or investigators about follow-up visits as outlined in the study schedule. If a volunteer is not compliant with a study visit, the study staff will actively attempt to contact the volunteer and document these attempts in the volunteer file.

